## 8.2. Determination of Sample Size

The trial will accrue 30 evaluable subjects in each Cohort, with or without confirmed c-MET amplification, as defined as  $\geq 3$  genomic copies of the *c-MET* gene. After the accrual of each cohort of 30 evaluable subjects, enrollment may be extended (to a maximum of 40 subjects) until at least eight subjects with confirmed c-MET amplification at 7q31, as defined as  $\geq 3$  genomic copies of the *c-MET* gene, are enrolled in each cohort. These will be stratified as follows:

- Stratum A: Subjects with confirmed *c-MET* amplification at 7q31.
- Stratum B: Subjects without confirmed *c-MET* amplification at 7q31

Additionally, as part of Amendment 4.0, there will be a requirement in Cohort 2 to have at least 4 evaluable subjects who meet a more stringent definition of *c-MET* gene amplification (i.e.  $\geq 2$  copies of *c-MET* per copy of chromosome 7; see Section 3.3.1 for a more detailed definition).

In the event that the enrolment of 30 evaluable subjects in Cohort 2 is completed before the target of 4 subjects with *c-MET* amplification, as defined by  $\geq 2$  copies of *c-MET* per copy of chromosome 7, has been reached, then extra subjects, with proven *c-MET* amplification, pre-screened by FISH, will be enrolled in the study, until the target is reached.

This sample size will allow an initial assessment of the tolerability of GSK1363089 in metastatic gastric cancer subjects, when dosed either in the intermittent 5&9 or daily schedules, building on the safety data from the two Phase I studies (77 subjects), which tested each of these schedules in subjects with a variety of solid tumors. Some hypothesis testing will also be possible with regards to the primary efficacy variable, which is the objective response rate (ORR), defined as the proportion of subjects for whom their best overall response is a confirmed CR or confirmed PR by RECIST:

For each Cohort, if at least 6 of the 30 evaluable subjects respond, this regimen of GSK1363089 will have demonstrated a response rate of 20%. This design is used to test the following hypothesis on the ORR:

Ho:  $P_o \leq 0.10$  versus  $P_a \geq 0.25$

Assuming a type I error rate (alpha) of 0.10 and a type II error rate (beta) of 0.20, with 30 evaluable subjects and at least 6 observed responses ( $\geq 0.20$ ) subjects, there is a 0.0732 chance of falsely concluding this regimen is preliminarily effective if the true response rate is 0.10. And the chance for falsely rejecting the effect of the regimen is 0.2026 if the true response rate is 0.25. If additional enrollment is required and at least 8 of the 40 ( $\geq 0.20$ ) evaluable subjects respond, then the above two probabilities would be 0.0419 and 0.18196, respectively.

With the design of this study, the following table (Table 7) summarizes the expected lower bounds for the 1-sided confidence interval corresponding to the 6/30 or 8/40 scenarios respectively, for each cohort.

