##### **3.1.1. Pre-Treatment Period**

Subjects will undergo evaluations to determine study eligibility. Screening will be conducted within 28 days before initial treatment on Day 1. The following baseline evaluations must be done within 72 hours of the initial treatment: physical examination, measurement of vital signs, the Eastern Cooperative Oncology Group (ECOG) performance status (Appendix B), hematology, serum chemistry panel, urinalysis, and a pregnancy test (in women of childbearing potential). In addition, the appropriate arrangements must be made to ensure that 10 unstained slides or a paraffin block of archived tumor tissue are shipped to the central analysis laboratory, no later than 14 days after the subject's first dose of study drug.

It is important to note that in the event that enrolment of 30 evaluable subjects in Cohort 2 is completed before the target of 4 subjects with *c-MET* amplification, as defined by  $\geq 2$  copies of *c-MET* per copy of chromosome 7 (see Section 3.3.1 for full definition), has been reached, then extra subjects, with proven *c-MET* amplification, pre-screened by FISH, will be enrolled in the study, until the target is reached. In this instance, 10 unstained slides or a paraffin block of tumor tissue must be shipped to the central analysis laboratory as soon as possible after the subject signs the consent form. The subject will not be able to start the study treatment period until FISH results are available, and then only if they have *c-MET*-amplified tumor, as defined by  $\geq 2$  copies of *c-MET* per copy of chromosome 7.

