**8.1.1. Analysis Populations**

The safety population will be defined as all subjects who received at least one dose of study drug.

The evaluable population will include subjects in the safety population who:

1. have a baseline and post-baseline tumor assessment, and
2. who have received at least 75% of protocol-mandated doses during the 8-week study treatment period;

as well as subjects who, prior to completing the 8-week Study Treatment Period:

1. require study drug discontinuation due to GSK1363089-related toxicity, or
2. have objective evidence of progressive disease.

All efficacy analyses will be performed on both the safety and the evaluable populations.

All safety analyses will be performed on the safety population.

All efficacy and safety analyses will be conducted on each cohort separately as well as together.

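### Cohort 2 may gain up to 4 evaluable subjects pre-selected for c-MET amplification, and nothing keeps them out of the primary ORR or provides a decision threshold for the enlarged cohort

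*Combined protocol and SAP*

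**What the plan says.** Section 8.2 accrues 30 evaluable subjects per cohort with or without c-MET amplification. Two separate rules can enlarge Cohort 2.

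- **Extension for the definition of at least 3 copies.** If fewer than 8 subjects qualify, "enrollment may be extended (to a maximum of 40 subjects" in the cohort). These added subjects are not described as pre-selected.
- **Top-up for the stringent definition** (at least 2 copies of c-MET per copy of chromosome 7; full criteria in 3.3.1). The target is 4 evaluable subjects. If it has not been met when 30 are evaluable, further amplified subjects, "pre-screened by FISH, will be enrolled in the study, until the target is reached". Section 3.1.1 makes this a condition of dosing: "The subject will not be able to start the study treatment period until FISH results are available". A subject whose tumour proves not to be amplified is not treated.

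On analysis, 8.1.1 states: "All efficacy analyses will be performed on both the safety and the evaluable populations". The safety population is everyone dosed. The evaluable population is defined by dosing, tumour assessment, drug-related toxicity and progression. Neither definition refers to c-MET status or route of enrolment. Section 8.1.1 also calls for analysis of the cohorts separately and together. Section 8.1.2 reports one crude ORR with an exact 95% interval per cohort.

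On the test, 8.2 sets 6 of 30 or 8 of 40 responses as the threshold. For 30 subjects it states that "there is a 0.0732 chance of falsely concluding this regimen is preliminarily effective if the true response rate is 0.10". It puts the type II error for 30 subjects, at a true rate of 0.25, at 0.2026. For 40 it gives 0.0419 and 0.18196.

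**The concern.** Every top-up subject is enrolled because the tumour is amplified. Section 3.3.1 introduces the stringent definition because gastric cell lines with true amplification were more sensitive to a c-MET inhibitor. If that carries over to patients, these subjects respond more often than the population the cohort is meant to describe.

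Pooled into the Cohort 2 ORR, they make it a mixture whose weights depend partly on the enrolment rule. The binomial error rates assume one common response rate and no longer apply.

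The plan also gives no threshold for 31-34 or 41-44 subjects. In an open-label study, the choice between keeping 6 and requiring 20% could be made after responses are known.

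**Working it through.** **1. Inputs from the documents.** Section 8.2: null rate 0.10, alternative 0.25, thresholds 6/30 and 8/40, and "Assuming a type I error rate (alpha) of 0.10 and a type II error rate (beta) of 0.20". The test is taken as one-sided: it asks for at least a given number of responses, and the text with Table 7 "summarizes the expected lower bounds for the 1-sided confidence interval". Sections 3.1.1, 3.3.1 and 8.2: the target is 4 evaluable amplified subjects, and every top-up subject is already amplified.

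**2. Assumptions.** The documents do not give the response rate q in stringently amplified subjects (10%, 25% and 50% shown) or the prevalence of stringent amplification (5%, 10% and 20% shown).

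**3. The plan's own figures.** With X binomial:
- n = 30: P(X ≥ 6 | 0.10) = 0.0732; P(X ≤ 5 | 0.25) = 0.2026.
- n = 40: P(X ≥ 8 | 0.10) = 0.0419; P(X ≤ 7 | 0.25) = 0.1820.

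All four reproduce, each with a single response rate for all subjects.

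**4. Size of the top-up.** The number of evaluable subjects added is m = max(0, 4 − amplified subjects already evaluable), so m ≤ 4. The largest share is 4/34 = 11.8%, or 4/44 = 9.1% after an extension to 40.

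**5. Expected pooled ORR**, with m = 4 added to 30 and a true unselected rate of 0.10: (30 × 0.10 + 4q)/34.
- q = 0.10: 3.4/34 = 10.0%
- q = 0.25: 4.0/34 = 11.8%
- q = 0.50: 5.0/34 = 14.7%

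**6. Type I error after pooling.** For threshold r, sum over j = 0 to 4 of P(Y = j) × P(X ≥ r − j), with X ~ Bin(30, 0.10) and Y ~ Bin(4, q). The tails P(X ≥ k) for k = 2 to 7 are 0.8163, 0.5886, 0.3526, 0.1755, 0.0732 and 0.0258. At q = 0.50 the weights P(Y = j) are 0.0625, 0.25, 0.375, 0.25 and 0.0625, so:
- r = 7: 0.0016 + 0.0183 + 0.0658 + 0.0882 + 0.0368 = 0.211
- r = 6: 0.0046 + 0.0439 + 0.1322 + 0.1472 + 0.0510 = 0.379

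| Amplified ORR q | Expected ORR | Type I, 7 of 34 (at least 20%) | Type I, count of 6 kept |
|---|---|---|---|
| 10% | 10.0% | 0.048 | 0.119 |
| 25% | 11.8% | 0.095 | 0.202 |
| 50% | 14.7% | 0.211 | 0.379 |

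Starting from 40 with m = 4 and q = 0.50, the expected ORR is (40 × 0.10 + 4 × 0.50)/44 = 13.6%. Type I error is 0.124 at 9 responses or 0.234 at 8.

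**7. Chance that a top-up is needed after 30.** P(Bin(30, prevalence) ≤ 3) = 0.94, 0.65 and 0.12 at prevalence 5%, 10% and 20%. The mean number added is 2.5, 1.3 and 0.2.

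**8. Averaged over that chance.** The table in step 6 is the largest top-up. Now let m vary, fix the overall unselected ORR at 0.10 and set q = 0.50. At 5% prevalence, type I error is 0.111 (20% rule) or 0.230 (6 kept), with expected ORR 13.1%. At 10% prevalence it is 0.077 or 0.124, with expected ORR 11.7%.

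**The case against.** The best case for the plan is that the rule is written as 6 of 30 or 8 of 40, and the top-up begins only after the 30 are complete. On a literal reading the test could be applied to those 30, where 0.0732 stands. That is a fair reading of the threshold, and it means that no section actually prescribes keeping 6 in a cohort of 34. But 8.1.1 and 8.1.2 define the ORR on all safety and all evaluable subjects, and nothing limits it to the first 30. The two parts remain unreconciled.

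The effect may also be small. It needs both a top-up and a higher response rate in amplified tumours, and the support for the latter is cell-line work with a different inhibitor. With 4 added and 7 responses required, type I error stays within 0.10 at q = 10% or 25%. At 20% prevalence a top-up is seldom needed. This stands, and it limits the claim about size.

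Section 3.3.1 already stratifies by the stringent definition, and 8.1 defers detail to a separate SAP that is not among the documents supplied and could settle the matter. Stratification does not change what enters the primary ORR.

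Three stronger readings are tempting, and the documents do not support them:

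- **The top-up is unlimited.** No maximum is stated, and the number dosed is open because non-evaluable subjects do not count toward the target. Evaluable additions stop at 4.
- **The top-up contradicts the maximum of 40.** That maximum belongs to the extension for at least 3 copies. The text leaves open whether the top-up falls inside or on top of it.
- **The top-up destroys comparability with Cohort 1.** The cohorts are sequential and non-randomized, they already differ in eligible histology and site (3.3.1), and the comparison of regimens is exploratory.

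**Conclusion.** The concern holds. As written, up to 4 evaluable subjects selected for amplification enter the Cohort 2 and combined ORR, while the error rates describe only 30 or 40 subjects sharing one response rate.

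The missing threshold is a defect even without any c-MET effect: with 4 added and q = 10%, the two natural choices give 0.048 and 0.119, on either side of the planned 0.10.

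The upward bias is conditional. With the full 4 added to 30, it is 0 to 4.7 percentage points in expected ORR across q = 10% to 50% (14.7% − 10.0% at the top). Those rates, and the prevalence that decides how often a top-up occurs, are assumptions. A reader might infer that the type I error is certainly inflated; the documents do not establish that.

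**What to change.** In 8.1.2 and 8.2, state that the primary Cohort 2 ORR, its confidence interval and the 6/30 (or 8/40) test use evaluable subjects enrolled without regard to c-MET status. Carry the same restriction into the headline combined ORR. Report the FISH-pre-screened subjects together with the other amplified subjects in the stringent-amplification stratum, and give a pooled ORR as a sensitivity analysis only. State whether the top-up falls inside or on top of the maximum of 40.

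At full accrual of 30 or 40 unselected evaluable subjects, this restores the stated error rates: 0.0732/0.2026 or 0.0419/0.182. The cost is protocol and SAP wording, and up to 4 evaluable subjects who do not count in the primary test. They still count toward the amplification target and the safety analysis.

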 Prior to Amendment 3.0, only subjects with poorly-differentiated gastric carcinoma or adenocarcinoma of the gastroesophageal junction were included. Amendment 3.0 expanded this, 1) to remove the requirement for poorly-differentiated histology, and 2) to include subjects with distal esophageal carcinoma.

regards to the primary efficacy variable, which is the objective response rate (ORR), defined as the proportion of subjects for whom their best overall response is a confirmed CR or confirmed PR by RECIST:

For each Cohort, if at least 6 of the 30 evaluable subjects respond, this regimen of GSK1363089 will have demonstrated a response rate of 20%. This design is used to test the following hypothesis on the ORR:

$$H_0: P_0 \leq 0.10 \text{ versus } P_a \geq 0.25$$

Assuming a type I error rate (alpha) of 0.10 and a type II error rate (beta) of 0.20, with 30 evaluable subjects and at least 6 observed responses ( $\geq 0.20$ ) subjects, there is a 0.0732 chance of falsely concluding this regimen is preliminarily effective if the true response rate is 0.10. And the chance for falsely rejecting the effect of the regimen is 0.2026 if the true response rate is 0.25. If additional enrollment is required and at least 8 of the 40 ( $\geq 0.20$ ) evaluable subjects respond, then the above two probabilities would be 0.0419 and 0.18196, respectively.

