### **Statistical Methods**

The primary efficacy endpoint is objective response rate (ORR). ORR will be estimated for the safety and the evaluable populations. A corresponding exact 95% confidence interval will be calculated.

Secondary efficacy endpoints are disease stabilization rate (DSR), progression-free survival (PFS), duration of stable disease, and duration of overall survival (OS). DSR will be summarized using a point estimate of the proportion and the exact 95% confidence interval. PFS, OS, and duration of stable disease will be summarized using Kaplan-Meier methods.

For the primary safety endpoint, AEs and serious adverse events (SAEs) will be tabulated by system organ class and preferred terms. Laboratory test results after the first dose will be summarized using change from baseline values and shift from baseline tables.

Each endpoint will be assessed both in the combined Cohorts and in each Cohort separately.

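### Reaching 6/30 responders rejects an ORR of 10% or less; it does not demonstrate 20%, and at 6/30, 7/30 or 8/40 the planned 95% interval still includes 10%

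*Combined protocol and SAP*

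**What the plan says.** For each cohort, Section 8.2 tests an ORR of at most 0.10 against at least 0.25, "Assuming a type I error rate (alpha) of 0.10 and a type II error rate (beta) of 0.20". To the threshold it attaches this conclusion: "if at least 6 of the 30 evaluable subjects respond, this regimen of GSK1363089 will have demonstrated a response rate of 20" per cent. The synopsis (Number of Subjects) has the same sentence: "this regimen of GSK1363089 will have demonstrated a response rate of 20" per cent.

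Section 8.2 then describes the same event more modestly: "there is a 0.0732 chance of falsely concluding this regimen is preliminarily effective if the true response rate is 0.10". For the other error it says that "the chance for falsely rejecting the effect of the regimen is 0.2026 if the true response rate is 0.25". The extended cohort has its own rule, which begins "If additional enrollment is required and at least 8 of the 40", with stated error probabilities 0.0419 and 0.18196. Table 7 "summarizes the expected lower bounds for the 1-sided confidence interval corresponding to the 6/30 or 8/40 scenarios".

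For the ORR analysis, the synopsis (Statistical Methods) says: "A corresponding exact 95% confidence interval will be calculated". Section 8.1.2 likewise plans a point estimate and an exact 95% interval per cohort. Neither place says whether the interval is one- or two-sided. Section 8.1.2 mentions neither the responder threshold nor a 90% bound.

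**The concern.** Two things do not fit together.

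- **The conclusion is stronger than the test.** Rejecting a null of 10% shows that the rate exceeds 10%. The plan says that the same result demonstrates 20%, which is the observed proportion at the threshold.
- **The test and the reported interval use different confidence levels.** The test is at one-sided 0.10. A two-sided 95% interval puts 0.025 in the lower tail. A cohort can pass the first and still have an interval that includes the null value.

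At stake is how a borderline cohort is read. One reader could cite the protocol for a demonstrated 20% rate. Another could point to a reported interval that reaches below 10%. The plan does not say which of the two governs.

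**Working it through.** **Inputs.** From Section 8.2: n = 30 with threshold 6; n = 40 with threshold 8; p0 = 0.10; p1 = 0.25; alpha 0.10; beta 0.20. The test is read as one-sided, from the form of the hypotheses and the 1-sided bounds of Table 7. The 95% interval is read as two-sided (assumption).

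**Step 1. Reproduce the stated error rates (exact binomial).** Type I error = P(X ≥ r | n, 0.10). Type II error = 1 − P(X ≥ r | n, 0.25).

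| Rule | Type I, computed | Stated | Type II, computed | Stated |
|---|---|---|---|---|
| ≥6/30 | 0.07319 | 0.0732 | 1 − 0.79740 = 0.20260 | 0.2026 |
| ≥8/40 | 0.04190 | 0.0419 | 1 − 0.81805 = 0.18195 | 0.18196 |

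The stated figures hold.

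**Step 2. What 6/30 supports.** The exact (Clopper-Pearson) lower bound with tail area a is the a-quantile of Beta(r, n − r + 1). With a = 0.10:

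- 6/30: 0.1086. This excludes 10% and is far below 20%.
- 9/30: 0.1899. 10/30: 0.2184. So the one-sided 90% bound passes 20% only from 10/30.
- With a = 0.025, 11/30 gives 0.1993 and 12/30 gives 0.2266. So the two-sided 95% interval passes 20% only from 12/30.

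**Step 3. The 95% interval around the threshold.** Its lower limit exceeds 10% only when P(X ≥ r | n, 0.10) is below 0.025.

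| Result | P(X ≥ r) at 0.10 | Exact two-sided 95% CI | Includes 10%? |
|---|---|---|---|
| 6/30 | 0.0732 | 7.7% to 38.6% | yes |
| 7/30 | 0.0258 | 9.93% to 42.3% | yes |
| 8/30 | 0.0078 | 12.3% to 45.9% | no |
| 8/40 | 0.0419 | 9.05% to 35.6% | yes |
| 9/40 | 0.0155 | 10.8% to 38.5% | no |

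If the 95% interval were one-sided, 6/30 would still include 10% (bound 9.1%), but 7/30 (11.5%) and 8/40 (10.4%) would not.

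**Step 4. How often it arises.** The share of rule-meeting cohorts whose two-sided 95% interval includes 10% is [P(X ≥ threshold) − P(X ≥ first count that excludes 10%)] / P(X ≥ threshold). At a true ORR of 0.25:

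- n = 30: (0.7974 − 0.4857) / 0.7974 = 39%.
- n = 40: (0.8180 − 0.7002) / 0.8180 = 14%.

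The same formula gives 58% and 28% at a true ORR of 0.20, and 89% and 63% at 0.10.

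**Step 5. Table 7 against exact one-sided bounds.**

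| | 90% | 95% | 97.5% |
|---|---|---|---|
| 6/30, Table 7 | 0.10427 | 0.0759 | 0.0506 |
| 6/30, exact | 0.1086 | 0.0909 | 0.0771 |
| 8/40, Table 7 | 0.1171 | 0.0925 | 0.0706 |
| 8/40, exact | 0.1201 | 0.1036 | 0.0905 |

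Table 7 is reproduced, to within 0.0001, by 0.20 − t × √(0.20 × 0.80 / n) with t on 29 degrees of freedom in both rows. These are not the exact limits planned in Section 8.1.2. In one cell the difference crosses 10%: at 8/40 the exact 95% bound is above 10%, as it must be when the attained level is 0.0419, but Table 7 puts it below.

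**Step 6. Does a 90% bound reproduce the rule?** At n = 30 it does: 5/30 has a bound of 8.3% and 6/30 has 10.9%. At n = 40 it does not. P(X ≥ 7 | 40, 0.10) = 0.0995, so 7/40 has an exact bound of 10.01%, yet it falls short of the 8-responder threshold.

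**The case against.** The case for leaving the plan alone has weight. Section 8.2 offers only limited hypothesis testing. It states the true hypotheses directly after the loose sentence, gives the attained 0.0732, and calls the conclusion preliminary. No calculation rests on the 20% sentence. No protocol action is tied to 6/30: Cohort 2 opens when Cohort 1 enrolment is complete, whatever its response count. A 0.10-level screen and a 95% interval answer different questions, and disagreement at the boundary is not in itself an error. Section 8.1 also leaves analysis details to a separate analysis plan, whose text is not in the material reviewed.

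This limits the consequence. It does not repair a sentence, given twice, that states a conclusion the test cannot support, nor does it say how the interval and the rule are to be read together.

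Three stronger readings are tempting, and the documents do not support them:

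- *Every successful cohort will report an interval that includes 10%.* This is confined to 6/30, 7/30 and 8/40. At a true ORR of 25%, 61% of rule-meeting cohorts of 30 and 86% of those of 40 would exclude 10%.
- *The 95% interval is the only planned inference.* Section 8.2 has a hypothesis, a threshold and error rates. Table 7 already shows the 90% bounds above 10% and the 95% and 97.5% bounds below it.
- *The real power is 0.486 (8/30) or 0.700 (9/40), not 0.80.* Those are powers of a different rule, that the 95% interval must exclude 10%. The plan claims about 0.80 only for its responder-count rule, and that claim reproduces.

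**Conclusion.** The point holds as a matter of wording and reporting alignment. The stated conclusion is wrong as written: 6/30 supports an ORR above 10%, with an exact one-sided 90% lower bound of 10.9%, and at least 10/30 would be needed to lift that bound above 20%. The interval mismatch is real but narrow. Sample size and error rates are sound.

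This rests on reading the test as one-sided, which the hypotheses and Table 7 imply, and the 95% interval as two-sided, which is usual but unstated. Under a one-sided 95% reading the mismatch shrinks to 6/30 alone. The check covers fixed cohorts of 30 and 40. Section 8.2 gives no threshold for sizes in between, or for Cohort 2 when pre-screened amplified subjects are added.

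**What to change.** 1. In the synopsis (Number of Subjects) and Section 8.2, replace the sentence on a demonstrated rate with: *At least 6/30 (or at least 8/40) responders rejects an ORR of 10% or less at nominal one-sided alpha 0.10 (attained 0.073 and 0.042). The observed rate is then at least 20%, but a true rate of 20% is not established.*
2. In Section 8.1.2, report the exact one-sided 90% lower bound beside the test (10.9% at 6/30, 12.0% at 8/40). State that the responder count decides, since 7/40 has a bound of 10.01% but does not meet the rule.
3. In Section 8.1.2 and the synopsis (Statistical Methods), state that the 95% interval is two-sided, if that is intended, and descriptive, and that it can include 10% at 6/30, 7/30 or 8/40.
4. Replace the Table 7 entries with the exact bounds in step 5 of the working, so that they agree with the exact interval that will be reported.

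Cost: a less favourable stated claim and one more interval in the output. No additional subjects or data are needed.
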